### Data collection

Table 1 gives an overview of time points for data collection in the proposed study.

**Table 1 T1:** Timeline of measurements in the study

Measurements	Screening	Randomisation	Intervention 1		3 months at home		Intervention 2	1 year
	Contact 1	Contact 2	Day 1 T=0*	Day 8* T=1*	Contact 3	Contact 4	Month 3 T=2*	Year 1 T=3
Primary outcomes								
PWS			X	X			X	X
NRS			X	X			X	X
Secondary outcomes								
MMQL			X	X			X	X
Physical activity			X	X			X	X
VO2max			X				X	
Blood pressure			X				X	
Heart rate			X				X	
Body mass index			X				X	
Adverse effects				X	X	X	X	X
Other data								
Willingness	X							
Preference	X							
Expectations	X							
Adherence				X			X	
Effectiveness		X			X	X		X
Demographic data	X							
Medical history		X						
Medication use		X			X	X		X
Other therapies/ self-care		X			X	X		X
Lifestyle changes		X			X	X		X
Supportive relationships		X			X	X		X
Self-efficacy outdoors		X			X	X		X
Outdoor activities		X			X	X		X
Physical activities		X			X	X		X

*To avoid possible effects of intervention-related expectations and anxiety and return euphoria, all self-reported questionnaires will be filled in by participants 2–3 weeks before the start of the first intervention, 2–3 weeks after intervention and 2–3 weeks after the second intervention. Willingness: participants’ willingness to be randomised, Preference: participants’ intervention preference, expectations: participants’ intervention expectations, Adherence: participants’ intervention adherence, Effectiveness: participants’ expected intervention the effectiveness.

MMQL, Minneapolis Manchester Quality of Life instrument; NRS, Nature Relatedness Scale; PWS, Psychological Well-being Scale; VO2max, maximal oxygen consumption.

The first part of this study has a follow-up time of 1 year. In addition to primary and secondary outcomes, other data will be collected for programme comparison, evaluation, study quality and reporting (see table 1). Lifestyle changes include diet, sleep, stress, physical activity (type, frequency/length), smoking, nicotine use, alcohol, caffeine and outdoor/nature activities (type, frequency/length). Supportive relationships concern the experienced relationships with others affected by cancer (scale 1–5, not at all to very much). Self-efficacy outdoors concern the confidence to spend time in nature/outdoors and their outdoor skills (scale 1–5, not at all to very much).

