### Sample size

The current study aims to recruit a total of 150 participants who will be randomised into two groups (n=75 per group). The power calculation is based on a two-group linear mixed-effects model for repeated measures data with attrition^38^ and provides 80% power to detect a medium-sized between-group difference (SMD=0.60). In the sample size estimation, we account for an attrition rate of 34.5% before the start of the intervention as reported in the previous pilot study^25^ and a low attrition rate (10%) during the intervention. The power calculation is based on a model with four repeated measurement points, a first-order autoregressive correlation structure, an initial repeated measures correlation of 0.60 (with decreasing magnitude of the repeated measures correlations with increasing distance between time points), an alpha level of .05, and a group allocation of 1:1.

The effect size estimates for the primary outcomes are based on a meta-analytical estimate^32^ of a standardised between-group difference of 0.69 (Hedges’ g) for interventions to enhance eudaemonic psychological well-being, and findings from a pilot study indicating a significant between-group difference in NRS between the wilderness programme and hotel stay (Cohen’s d=0.63).^25^

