### Randomisation and concealment

Participants will be randomised equally (1:1) to the wilderness programme or hotel stay according to a randomisation list as generated by a Random Allocation Software Programme^40^ using a random block size of two to guarantee a balanced allocation. Participants will be stratified according to two age groups (16–30, 31–39 years), binary gender categorisations (male/female) and cancer survivorship (childhood cancer: age 0–14 years vs AYA cancer: age 15–39 years) to achieve equal distribution among the two groups. Per stratification and per country (Norway, Sweden), separate randomisation lists will be generated. AYAs affected by cancer who have registered their interest in the study via the website will receive a screening number based on the date of registration entry. Eligible participants will be randomised and assigned to the wilderness programme or hotel stay based on the fixed order of the screening numbers by a researcher who is not involved in the screening and intake of study participants. Allocation to programme intervention will be concealed by the complexity of the randomisation procedure involving a group of ten or more eligible participants at a time and randomisations over eight different strata during the period of 1 year.

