### Blinding

On screening, participants will be informed that two possibly effective programmes will be investigated. To reduce expectation bias, it will not be made known to participants whether the wilderness programme is hypothesised to be better than a hotel stay (single blinded). Statistical analysis will be performed by a statistician who is blind to programme allocation.

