### Data analysis

χ^2^ statistics, independent samples t-tests and analysis of variance will be used to calculate group differences in sociodemographic variables and cancer characteristics at baseline. The alpha level will be set to 0.05. The primary analysis will investigate changes in the total scores of the PWS and NRS over time from baseline to 1- year follow-up in the intervention group compared with the control group. Missing data will be imputed by means of multiple imputations or by using full-information maximum likelihood estimation.^41^ The analysis of the primary outcome will be based on a linear mixed-effects model and will be fitted to test intervention effects up to 1 year. Adjustments will be made for age, gender, age at cancer diagnoses and study site. Time, intervention arm, interaction between time and intervention arm, age, gender, age at cancer diagnoses and study site are included as fixed effects, and the participant is included as random effect in the model. Statistical analyses will be on the intention-to-treat principle (all participants who are randomised in the study). As sensitivity analyses, the per-protocol data set will be analysed including only participants who have participated for at least 1 day in the wilderness or hotel stay. Secondary outcomes will also be analysed using linear mixed-effects models.

Categorical data will be presented as frequencies and percentages. For continuous data, the number, mean, SD, median, IQR, minimum and maximum will be calculated. A two-sided p<0.05 will be considered statistically significant.

Safety analyses will be performed on the safety analysis set and include all individuals who had participated in one of the programme interventions for at least 1 day. RR with 95% CI will be calculated to indicate the risk of having an AE adjusted to days of exposure to programme interventions. Pearson’s χ^2^ test will be used to calculate differences in AEs severity between the two study arms. A detailed description of the planned statistical analyses will be provided in the statistical analysis plan, which will be finalised prior to database closure and data analysis. All statistical analyses will be performed by using Stata V.18.0.

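### The baseline PWS, NRS and MMQL scores are collected after randomisation and probably with allocation known, so the change-from-baseline contrast is open to an avoidable bias and some early leavers will have no primary-outcome score

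*Protocol article*

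**What the plan says.** Table 1 in the Data collection section of the protocol article orders the contacts as "Screening Randomisation Intervention 1". PWS, NRS and MMQL have no mark under Screening (Contact 1) or Randomisation (Contact 2); their first mark is at T=0. The footnote states that "all self-reported questionnaires will be filled in by participants 2–3 weeks before the start of the first intervention", and gives the reason: "To avoid possible effects of intervention-related expectations and anxiety and return euphoria". The lead time is therefore counted back from departure, not from randomisation.

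Randomisation and concealment describes allocation in groups of ten or more eligible participants, with "randomisations over eight different strata during the period of 1 year". Under Blinding, what is withheld from participants is the study hypothesis: "it will not be made known to participants whether the wilderness programme is hypothesised to be better than a hotel stay (single blinded"). That section does not say that the allocated programme is withheld, or when it is disclosed.

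Under Data analysis, "The primary analysis will investigate changes in the total scores of the PWS and NRS over time from baseline to 1- year follow-up", using a linear mixed-effects model with time, arm and their interaction as fixed effects, on all randomised participants. Baseline score is not among the listed covariates. Under Sample size, "we account for an attrition rate of 34.5% before the start of the intervention", plus 10% later.

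**The concern.** PWS, NRS and MMQL are self-reported. A participant who has been told that a wilderness expedition or a spa-hotel stay lies ahead may answer differently because of that news. If the arms differ in this way at T=0, the baseline is no longer a pre-treatment quantity that randomisation has balanced, and a comparison of changes from it carries the imbalance. The protocol recognises that expectations and anxiety can affect these questionnaires, but its remedy moves them away from departure without placing them before allocation.

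A second consequence does not depend on disclosure. Anyone who leaves after randomisation but before the questionnaire date has no PWS or NRS score at any time, although the analysis is meant to include everyone randomised. Whether leavers differ between arms on the primary outcomes then cannot be examined.

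The timing of the baseline is fixed in this document. No later analysis plan can recover a score that was not collected before randomisation.

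**Working it through.** **1. Who the 34.5% applies to.** Inputs from Sample size and Data analysis: SMD 0.60, 80% power, two-sided alpha 0.05, 10% attrition during the intervention, 34.5% before it.

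- Per arm before attrition: 2 × (1.960 + 0.842)² / 0.60² = 43.6, so 44.
- After 10%: 44 / 0.90 = 48.9, so 49.
- After 34.5%: 49 / 0.655 = 74.8, so 75 per arm, 150 in total.

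The plan's figure is reproduced, so the 34.5% is a loss among those randomised. The sample size itself is not in question here.

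**2. Expected early leavers.** 150 × 0.345 = 51.75, about 52 (26 per arm); 150 × 0.655 = 98.25, about 98, reach the start. Those who leave in the last 2–3 weeks may already have completed T=0, so 52 is a ceiling on the number with no PWS or NRS score.

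**3. How a baseline shift enters the primary contrast.** The power model has four measurement points, which match T=0 to T=3, and baseline is not a listed covariate. Baseline is thus read as one of the repeated outcomes. Let d0 be the allocation-driven difference (wilderness minus hotel) at T=0 and d1 the part of it still present at follow-up. The change contrast is then

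true effect + d1 − d0.

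If the shift persists in full (d1 = d0), it cancels. If it has gone by follow-up (d1 = 0), the bias is −d0. The bias always equals the part that does not persist.

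**4. Illustrative size.** The documents give no value for the shift, so the values below are assumptions, and the shift is taken to have gone by year 1. The error rate is for a change-score test with 44 per arm. The baseline-to-year-1 correlation under the protocol's AR(1) 0.60 is 0.6³ = 0.216. The change variance is 2 × (1 − 0.216) = 1.568 SD², and the standard error is √(2 × 1.568 / 44) = 0.267 SD.

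| Non-persisting shift (SD) | Share of 0.60 | Two-sided error with no true effect |
|---|---|---|
| 0.05 | 8% | 5.4% |
| 0.10 | 17% | 6.6% |
| 0.20 | 33% | 11.6% |
| 0.30 | 50% | 20.3% |

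**5. What a baseline score would add for an early leaver.** 0.216² = 0.047: baseline explains about 5% of year-1 variance under the protocol's own correlation structure. It allows leavers to be described and compared by arm, but says little about their year-1 outcome.

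**The case against.** **Disclosure is inferred.** A reader might infer that the protocol has participants complete T=0 knowing their programme. It does not say so. The inference rests on the column order, on Contact 2 being a participant contact at randomisation that records expected effectiveness, and on blinding to the hypothesis only. It is a strong inference, but if disclosure in fact follows the questionnaire, the expectation argument falls and a clarifying sentence is enough on that part. The missing scores of early leavers would remain.

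**The shift need not pass fully into the result.** Participants stay aware of their programme throughout, and any persisting enthusiasm or disappointment cancels in the change. This stands, and the bias is limited accordingly.

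**The direction may be conservative.** If the wilderness is preferred, anticipation there and disappointment in the hotel arm would both make the wilderness effect look smaller. Anxiety before the expedition would act the other way, and the 2–3-week lead is meant to reduce it. The documents do not settle which dominates, so a reading that the design favours the wilderness programme is not supported.

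**Missing baselines do not by themselves undo the all-randomised analysis.** With about 5% of year-1 variance explained, a baseline alone contributes little for someone who leaves before the start. Imputation already has covariates from Contacts 1 and 2, and the power loss is built into the 150. This stands.

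**An early baseline has a price.** Enrolment began on 19 February 2024 for summer 2024 interventions, and randomisation runs over a year. A score taken at screening could be months old in people at very different stages of treatment. This also stands and bears on when the questionnaire should be collected.

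**Conclusion.** The point holds as a schedule weakness that can be corrected at low cost. The baseline for both primary outcomes and for MMQL follows randomisation and probably follows knowledge of allocation. The part of any allocation-driven shift that fades before follow-up biases the arm-by-time contrast one for one, in an unknown direction. The 17–33% of the planned effect is arithmetic on an assumed 0.1–0.2 SD, not an estimate for this trial. Up to about 52 of 150 randomised participants could have no PWS or NRS score; the true number depends on how many leave before the questionnaire date. The conclusion rests on reading Table 1's columns in time order and on baseline entering the model as a repeated outcome.

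**What to change.** For participants not yet randomised, collect PWS, NRS and MMQL after consent and before the randomisation batch is run, or at least before allocation is disclosed, and as close to randomisation as practical. Define these scores as the baseline. The 2–3-week pre-departure questionnaire can stay as an additional post-randomisation measure. State in the protocol when allocation is disclosed.

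For participants already randomised, flag the baseline as post-randomisation and run a sensitivity analysis. One option is to compare the arms at follow-up with T=0 left out of the outcome vector, adjusting for covariates recorded before randomisation. With equal variances and the protocol's correlation, this loses no precision against a simple change score: the variance is 1 SD² against 1.568.

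Costs: an amendment to the measurement schedule; a longer and more variable interval from baseline to intervention; and a baseline definition that differs between early and later participants, largely Sweden (summer 2024) against Norway (summer 2025). Randomisation lists are separate by country, so a shift common to both arms within a country cancels in the arm contrast. The study-site term and the sensitivity analysis should address the rest. The change lets early leavers be compared by arm at baseline; it does not recover their missing follow-up outcomes.

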### Sample size

The current study aims to recruit a total of 150 participants who will be randomised into two groups (n=75 per group). The power calculation is based on a two-group linear mixed-effects model for repeated measures data with attrition^38^ and provides 80% power to detect a medium-sized between-group difference (SMD=0.60). In the sample size estimation, we account for an attrition rate of 34.5% before the start of the intervention as reported in the previous pilot study^25^ and a low attrition rate (10%) during the intervention. The power calculation is based on a model with four repeated measurement points, a first-order autoregressive correlation structure, an initial repeated measures correlation of 0.60 (with decreasing magnitude of the repeated measures correlations with increasing distance between time points), an alpha level of .05, and a group allocation of 1:1.

The effect size estimates for the primary outcomes are based on a meta-analytical estimate^32^ of a standardised between-group difference of 0.69 (Hedges’ g) for interventions to enhance eudaemonic psychological well-being, and findings from a pilot study indicating a significant between-group difference in NRS between the wilderness programme and hotel stay (Cohen’s d=0.63).^25^

### Recruitment

Participants will be recruited among members of the Swedish cancer organisations Ung Cancer and the Childhood Cancer Fund, members of the Norwegian cancer organisation Ung Kreft and through oncology departments of hospitals in Norway and Sweden. In all news items, information and brochures, AYAs are directed to the website of the WAYA-2 study where they can register their interest in possible participation in the study.^39^

### Randomisation and concealment

Participants will be randomised equally (1:1) to the wilderness programme or hotel stay according to a randomisation list as generated by a Random Allocation Software Programme^40^ using a random block size of two to guarantee a balanced allocation. Participants will be stratified according to two age groups (16–30, 31–39 years), binary gender categorisations (male/female) and cancer survivorship (childhood cancer: age 0–14 years vs AYA cancer: age 15–39 years) to achieve equal distribution among the two groups. Per stratification and per country (Norway, Sweden), separate randomisation lists will be generated. AYAs affected by cancer who have registered their interest in the study via the website will receive a screening number based on the date of registration entry. Eligible participants will be randomised and assigned to the wilderness programme or hotel stay based on the fixed order of the screening numbers by a researcher who is not involved in the screening and intake of study participants. Allocation to programme intervention will be concealed by the complexity of the randomisation procedure involving a group of ten or more eligible participants at a time and randomisations over eight different strata during the period of 1 year.

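### Fixed blocks of two within stratum-by-country lists leave some allocations certain in advance, and procedural complexity does not conceal them

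*Protocol article*

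**What the plan says.** All of this is in the protocol article under Randomisation and concealment, unless another section is named.

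- Ratio and blocks: "Participants will be randomised equally (1:1) to the wilderness programme or hotel stay", from a computer-generated list, "using a random block size of two to guarantee a balanced allocation".
- Strata: "Participants will be stratified according to two age groups (16–30, 31–39 years), binary gender categorisations (male/female) and cancer survivorship" (childhood versus adolescent and young adult cancer).
- Lists: "Per stratification and per country (Norway, Sweden), separate randomisation lists will be generated".
- Order and assigner: eligible people are assigned "based on the fixed order of the screening numbers by a researcher who is not involved in the screening and intake of study participants". The screening number follows the date of registration on the website.
- Concealment: "Allocation to programme intervention will be concealed by the complexity of the randomisation procedure", described as "involving a group of ten or more eligible participants at a time and randomisations over eight different strata during the period of 1 year".

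Under Blinding, what is withheld from participants is whether one programme is expected to do better. They necessarily know which programme they attend. The statistician is blind to allocation.

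**The concern.** Concealment means that nobody who influences entry can foresee the next assignment. With blocks of two, the second member of each pair always receives the arm that the first did not. The word random in front of the block size adds nothing, because only one size is named, and that size is now published.

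Four facts place a person in a list: age group, gender, age at diagnosis and country. All are known at intake. Earlier allocations can be seen, since one group goes on an expedition and the other to a spa hotel. Anyone who follows a stratum's sequence can therefore tell whether its current pair is half-filled and, if so, what comes next. Having many strata and batches makes this laborious, but it keeps nothing secret.

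What is at stake is selection. A decision on eligibility or intake, or a discouraging conversation, could be influenced by a foreseeable arm. Both primary outcomes are self-report scales, and Table 1 has participants' preferences and expectations recorded at screening, before randomisation. Staff may thus know a candidate's preference and be able to work out the arm.

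**Working it through.** **Inputs from the protocol article.** Block size 2, ratio 1:1, three two-level factors, two countries, batches of at least 10 (Randomisation and concealment); 150 participants (Sample size); programme groups of 10–12 (Intervention group and Control group sections).

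**Assumptions not in the document.** 75 participants per country, eight equally likely strata per country, constant batch size b. Batches of 20 and 24 are included because they would fill one wilderness and one hotel group of 10–12 each.

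**Number of lists.** 2 × 2 × 2 = 8, which reproduces the stated eight strata. With separate lists per country, 8 × 2 = 16 lists, or 150/16 ≈ 9.4 people per list.

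**One-at-a-time limit.** The second member of each pair is fixed, so the share approaches 50% and the correct-guess rate approaches 0.5 × 0.5 + 0.5 × 1 = 75%. About four of the eight lists in a country end on an odd count, so the share is (75 − 4)/2 = 35.5 of 75 ≈ 47%, and the guess rate is 0.5 + 0.5 × 0.47 ≈ 74%.

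**Under the planned batching.** An allocation is certain before the batch only if its list is half-filled at that moment and the person is the first from that list in the batch. After n people in a country, the chance that a given list is half-filled is [1 − (3/4)^n]/2. The chance that a batch of b contains someone from that list is 1 − (7/8)^b. The expected number fixed in one batch is 8 times the product.

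For b = 10 (seven batches of 10, then one of 5):
- first batch: 0
- second (n = 10): 8 × 0.737 × 0.472 = 2.78
- third (n = 20): 8 × 0.737 × 0.498 = 2.94
- fourth to seventh: 4 × 8 × 0.737 × 0.5 = 11.79
- last batch of 5: 8 × 0.487 × 0.5 = 1.95
- total: 19.46 of 75 ≈ 26%

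The same sum for other batch sizes, with guess rate = 0.5 + 0.5 × share:

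| Batch size | Fixed beforehand | Guess rate |
|---|---|---|
| 10 | 26% | 63% |
| 12 | 23% | 61% |
| 20 | 14% | 57% |
| 24 | 12% | 56% |

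Simulation gives the same values. With moderately unequal strata the shares are about 22%, 20%, 13% and 11%.

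**With randomly varied blocks of 2, 4 and 6.** In simulation under the same assumptions, with an observer who knows the possible sizes, allocations known with certainty fall to about 2% for batches of 10 and about 1% for batches of 20–24. The average guess rate changes little. For batches of 10 it goes from 63% to about 60–62%. For batches of 20 it goes from 57% to about 56–58%. The range depends on whether the observer also guesses for second and later members of a stratum within a batch. The mean absolute difference between arms is about 2.3 participants per country, against 1.7 with blocks of two.

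**The case against.** The protocol contains real safeguards. Ten or more people are randomised together, so both members of a pair often fall in the same batch and neither is known beforehand. People register themselves, and allocation follows registration order, so staff have little scope to move someone to a chosen slot. The assigner is separate from screening and intake, and nothing says that intake staff see the lists. The two medical exclusions rest on the treating physician or oncologist, and willingness to be randomised is the participant's own decision. Varying the blocks also barely alters the average guess rate.

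Most of this stands, and it rules out several stronger readings. A reader might infer that half of all allocations (75 of 150) are predictable, with a 75% guess rate. Those are limits for randomising one person at a time, which is not the plan. A reader might also infer that strong preferences carry selection straight into the outcomes. The document shows only that preference is recorded, not how strong it is. Nor does anything show that a prediction was used, or that the list was open to recruiting staff.

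What does not follow is that allocation is concealed. The fixed order applies to people found eligible, and when eligibility is settled can decide which batch a person joins. Separating the assigner protects the list, but with blocks of two the next assignment can be worked out without it. The small change in the guess rate is correct, but the gain from varied blocks lies in removing certainty.

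**Conclusion.** The point holds at a moderate size. The stated mechanism does not deliver concealment, because the next allocation in any half-filled pair can be deduced with certainty by someone who follows the stratum. Under the planned batching this affects roughly one allocation in four with batches of 10 (0.26 × 150 ≈ 39 people) and roughly one in eight with batches of 24 (0.12 × 150 = 18 people). These figures rest on an even country split, equal strata and constant batch size; unequal strata lower them slightly. They also assume an observer who knows every earlier allocation in the stratum, so they are upper values for what staff would in practice know.

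The remaining route to bias is narrow: an eligibility or intake decision, or discouragement, for a person next in a half-filled pair. The sample size is unaffected.

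**What to change.** For lists not yet used, generate permuted blocks of randomly varying size (such as 2, 4 and 6) and do not disclose the sizes. Norway is the likely case, since its interventions were planned a year after the first Swedish ones (Timeline of the study). Keep the lists and the earlier allocations by stratum with the independent assigner, away from screening and intake staff. In the protocol, replace the statement that complexity conceals allocation with this access restriction, drop the word random from the description of a single block size, and state that there are 16 lists.

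If every list has been used, the block change is no longer possible. The sponsor can still document who held the lists and who could see earlier allocations.

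The cost is regenerating the unused lists and slightly more chance imbalance (about 2.3 versus 1.7 participants per country on average). The adjustment for age, gender, age at diagnosis and study site already planned under Data analysis covers this. Slightly less even numbers also have to fit programme groups of 10–12.
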